### Analysis

Differences in the primary and secondary outcomes between the three groups will be determined using non-parametric tests. Multi-group differences in the rate of pharmacotherapy escalation will be determined using the Kruskal-Wallis test. Differences in the proportion of participants with disease progression will be compared using the Cochran-Mantel-Haenszel test with continuity correction. Two-group differences will be tested using the Wilcoxon Rank Sum (Mann–Whitney U) test. Correction for multiple comparisons will be conducted using the Tukey method.

The primary analysis population will be intent-to-treat. As-treated and per-protocol study populations will also be reported. In the intent-to-treat analysis, the minimization algorithm will be preserved and dropouts will be assumed to have had no progression post-dropout. In the as-treated analysis, patients misallocated relative to the minimization algorithm will be analyzed per the intervention received. In the per-protocol analysis, misallocated participants and other protocol violations specified prior to breaking the blind will be omitted. Complete and Markov chain Monte Carlo multiple imputed data will be reported. The goal of analyzing across different analysis sets is to demonstrate robust study results across the various alternatives. All statistical analyses will be conducted using SAS/STAT version 9.2 (Cary, NC, USA).

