### Randomization

Minimization (that is, baseline adaptive randomization) will be used to allocate participants to one of the three study interventions. Allocation by minimization is recommended for small sample size clinical trials in diseases with many known prognostic markers [41,42]. The minimization procedure can accommodate 10 to 20 variables without sacrificing statistical power [71,72]. Parameters for minimization will include the following:

● Participant self-reported symptom duration (<6, 6-24, >24 months)

● Baseline 28-joint Disease Activity Score (<2.6, 2.6-3.2, 3.2-5.1, >5.1)

● MRI or X-ray evidence of erosions from the hands, wrists or feet at baseline

● Rheumatoid factor positivity (positive; negative; not available)

● Anti- citrullinated cyclic peptide positivity (positive; negative; not available)

● Extra-articular features of RA

● Health Assessment Questionnaire

● Conventional DMARD treatment

● Biologic DMARD treatment

● Treating rheumatologist

With the exception of 'treating rheumatologist', these variables have prognostic value and are expected to inform DMARD treatment decision-making [43]. ‘Treating rheumatologist’ will be included as a minimization parameter to balance the effect of varying pharmacological disease management standards of care by physician across the three study groups.

Minimization will be conducted using a SAS (Cary, NC, USA) macro (Additional file 1). The generic two-group SAS macro for minimization [73] was adapted into the three-group algorithm by [name] and [name] (personal communication, March 2011).

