The estimated standard deviation around disease progression-related treatment escalation rates was assumed to vary proportionally the variance around disease progression. From Emery and colleagues (2009), an average standard deviation of 5% greater magnitude than the mean progression was determined for group sample sizes of approximately 200 [75]. Standard deviation is inversely related to . A sample size 25% greater than the mean effect size reported in Emery was estimated here. Therefore, *δ* ≈ 0.46 and *s* ≈ 0.58, *f* ≈ 0.33. This represents a sample size of ≈ 45 per group [74] unadjusted for spontaneous remission, attrition and missing data. Despite the liberal inclusion criteria used here, with the current setting characterized by patients with significantly progressed symptom duration, spontaneous remission was conservatively estimated at 5%. Missing data and annual attrition were estimated to be 15% and 5%, respectively. Given these estimates, a sample size of 62 participants per intervention allocation group will be required to determine a 36% difference in the rate of treatment escalation with 90% power at a 5% level of significance [74,76]. A total of 186 IA patients will be recruited by six participating rheumatologists.

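### The primary comparison of escalation ignores the ten minimisation factors, so the test is valid but conservative and gives up power that an adjusted analysis would keep

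*Protocol article*

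**What the plan says.** The Analysis section names the test for the primary outcome: "Multi-group differences in the rate of pharmacotherapy escalation will be determined using the Kruskal-Wallis test". For pairs it says: "Two-group differences will be tested using the Wilcoxon Rank Sum (Mann–Whitney U) test". No covariates, strata or adjusted model are named for escalation. Progression, the co-primary endpoint, is compared by a Cochran-Mantel-Haenszel test, again with no strata named.

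The Randomization section says that minimisation "will be used to allocate participants to one of the three study interventions" and lists ten parameters: symptom duration, DAS28, erosions, rheumatoid factor, anti-CCP, extra-articular features, HAQ, conventional DMARD, biologic DMARD and treating rheumatologist. Of the first nine it says that "these variables have prognostic value and are expected to inform DMARD treatment decision-making". Treating rheumatologist "will be included as a minimization parameter to balance the effect of varying pharmacological disease management standards of care by physician". The section also asserts: "The minimization procedure can accommodate 10 to 20 variables without sacrificing statistical power".

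The intent-to-treat paragraph says that the minimised allocation is to be kept. It is set against an as-treated analysis that follows the intervention received, so it means analysis by allocated arm. It does not describe covariate adjustment.

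**The concern.** The primary outcome is a DMARD treatment decision, and the protocol itself says the minimisation factors inform such decisions or account for differences between physicians. By its own reasoning, then, the factors explain some of the outcome.

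Minimisation removes most of the chance imbalance in those factors, so under the null the arms differ less than under simple randomisation. Kruskal-Wallis and Wilcoxon still judge the difference against the full spread of the ranks, including the part the factors explain. The reference distribution is too wide and the test rejects too seldom.

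What is at stake is sensitivity. The Discussion warns that background escalation under usual care may drown the effect of the imaging reports. It also concedes that the sample size did not specifically account for such escalation. Adjusting for rheumatologist, disease activity and baseline therapy would remove part of that noise with data already collected at baseline.

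**Working it through.** **Step 1: the plan's own figure.** The Sample size section uses a one-way ANOVA with three groups, δ ≈ 0.46 and s ≈ 0.58, at "with 90% power at a 5% level of significance".
- Its formula (3) gives f = (0.46/0.58)/2 × √(4/6) = 0.324, stated as about 0.33.
- The noncentral F distribution then needs 42 per group, or 44 after dividing by the rank-test efficiency 0.955. The plan states about 45.
- Inflating for 5% remission, 15% missing data and 10% attrition over two years gives 45/(0.95 × 0.85 × 0.90) = 61.9, so 62 per group.

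The 62 reproduces, and the calculation takes no credit for covariates.

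**Step 2: true size under perfect balance.** Let R² be the share of variation in the ranked outcome explained by the factors. The documents give no value, so it is varied. With the factors balanced, the between-arm variance carries only 1 − R² of the total, while the test divides by the total. The statistic then behaves as (1 − R²) times a chi-square on 2 df:

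size = P(χ²₂ > 5.991/(1 − R²))

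- R² = 0.1: 5.991/0.9 = 6.657, size 3.6%
- R² = 0.2: 5.991/0.8 = 7.489, size 2.4%
- R² = 0.3: 5.991/0.7 = 8.559, size 1.4%

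**Step 3: simulated minimisation.** Real minimisation does not balance perfectly, so it was simulated: 186 patients, three arms, deterministic minimisation on ten factors, 40,000 replicates. Assumptions were equally frequent factor levels, HAQ in three levels, a normal outcome, and a 0.63 SD shift between extreme arms for power. The comparator is a rank analysis of covariance on all ten factors.

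| Assumed R² | Size, Kruskal-Wallis | Size, adjusted | Power, Kruskal-Wallis | Power, adjusted | Power gap (points) |
|---|---|---|---|---|---|
| 0 | 4.9% | 5.0% | 86.9% | 86.4% | −0.5 |
| 0.1 | 3.6% | 4.9% | 87.3% | 89.5% | 2.2 |
| 0.2 | 2.7% | 5.1% | 88.3% | 92.8% | 4.5 |
| 0.3 | 1.7% | 5.1% | 89.1% | 95.5% | 6.4 |

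The conservatism is not peculiar to a normal outcome. With Poisson counts (assumed background of 1.5 escalations per two years, log-rate SD of 0.5 from the factors, no dropout), Kruskal-Wallis ran at 2.1% and the adjusted analysis at 5.0%.

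**Step 4: the gap in patients.** Let λ be the noncentrality of the unadjusted test under simple randomisation: 11.54 for 87% power, 12.65 for 90%. Under balance both tests have noncentrality λ/(1 − R²). The adjusted test uses the cut-off 5.991 and the unadjusted test uses 5.991/(1 − R²). The multiple of patients at which the unadjusted test matches the adjusted one is:
- R² = 0.1: 1.08, about 8% more
- R² = 0.2: 1.16 to 1.17, about 16–17% more
- R² = 0.3: 1.25 to 1.26, about 25–26% more

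**Step 5: size of the adjusted model.** Entering symptom duration, DAS28 and HAQ as measured takes 3 coefficients. Erosions, extra-articular features, conventional DMARD and biologic DMARD take 4. Rheumatoid factor and anti-CCP, at three levels each, take 4. Six rheumatologists take 5. With 2 for arm the total is 18, or 186/18 ≈ 10 patients per coefficient. The simulation in Step 3 entered every factor as categories (20 coefficients plus 2 for arm) and still held its size.

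**The case against.** The strongest defence is that nothing here makes the primary test invalid. Its error is in the safe direction, and the trial was sized on an unadjusted analysis. Kruskal-Wallis power under minimisation even rises slightly with R², from 86.9% to 89.1% in the simulation. That stands. A reader might infer that false positives are inflated, or that the planned 90% is compromised by this choice. Neither follows: the loss exists only relative to an adjusted analysis. The protocol's statement that minimisation costs no power is likewise not contradicted.

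A reader might also put the gain at 1/(1 − R²), that is 11%, 25% or 43% more patients. That figure compares adjustment with an unadjusted test under simple randomisation. Here minimisation has already reduced the variance of the comparison, and only the yardstick is wrong, so the figures in Step 4 apply. Nor can it be said that confidence intervals will be too wide, since the section specifies none.

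Another tempting inference is that the rule "dropouts will be assumed to have had no progression post-dropout" biases the escalation comparison. The rule is worded for progression. The same section also reports complete-case and multiply imputed results. The Sample size section expects 5% annual attrition with no difference by arm, and allocation is concealed. With 10% dropout in every arm, the simulated count scenario gave a Kruskal-Wallis size of 2.4%, against 2.1% without dropout. The documents do not support a charge of differential dropout.

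Finally, an article may leave strata and supportive models to the analysis plan. That is fair for the Cochran-Mantel-Haenszel strata. It does not cover the escalation test, which the article positively names and which cannot carry the factors.

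**Conclusion.** The point holds as a matter of efficiency. An unadjusted rank test after minimisation on ten factors, which the protocol regards as prognostic or as sources of variation in care, is valid but conservative. For R² of 0.1, 0.2 or 0.3, its true size is about 3.6%, 2.4–2.7% or 1.4–1.7%. It forgoes about 2, 4.5 or 6 power points, equivalent to about 8%, 16% or 25% more patients.

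The direction rests on the protocol's own description of the factors. The size rests on R², which the documents do not give, and on the simulation's assumed shift and factor distributions. If the factors explain nothing, there is no loss. The planned power and the validity of a positive result are unaffected. The practical risk is that a real effect of imaging reports is missed because the test is stricter than its stated level.

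**What to change.** Before unblinding, name a primary analysis of escalation that adjusts for the minimisation factors, including treating rheumatologist. Rank analysis of covariance stays closest to the present non-parametric plan; a count model with robust variance is an alternative. Enter DAS28, HAQ and symptom duration as measured where possible. State in advance a reduced covariate list and the condition for using it, because all factors plus arm take about 18 coefficients in 186 patients. Make pairwise comparisons from the same adjusted analysis, and keep Kruskal-Wallis and Wilcoxon as sensitivity analyses.

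For progression, either name key minimisation factors as strata in the Cochran-Mantel-Haenszel test or adjust for them in a model.

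The cost is wording and a little programming. All the covariates are baseline data that the minimisation already requires. If the factors prove not to be prognostic, the power cost is about half a point (86.4% against 86.9%).

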### Outcomes

#### Primary outcome

The primary outcome of the study is DMARD treatment augmentation over 2 years. All changes in DMARDs and/or biologic treatment over the course of the study will be recorded. The primary endpoint definition is any change in DMARD agent or dose escalation. A co-primary endpoint is diagnostic imaging evidence of disease progression. Clinical radiology reports of the disease progression from discretionary diagnostic imaging requisitions will count towards the assessment of the co-primary endpoint.

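### The primary intent-to-treat analysis counts dropouts as non-progressing after they leave, which lowers the co-primary progression proportions and treats unobserved outcomes as known

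*Protocol article*

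**What the plan says.** The Analysis section sets the population: "The primary analysis population will be intent-to-treat". It then attaches a rule for those who leave: "In the intent-to-treat analysis, the minimization algorithm will be preserved and dropouts will be assumed to have had no progression post-dropout". No reason for the rule is given.

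The rule bears on a main result. Under Primary outcome: "A co-primary endpoint is diagnostic imaging evidence of disease progression". The Analysis section compares the proportion progressing between groups with a Cochran-Mantel-Haenszel test.

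The same Analysis paragraph adds: "Complete and Markov chain Monte Carlo multiple imputed data will be reported". It does not say which analysis set these results belong to, or how they rank against the dropout rule. The stated purpose is general: "The goal of analyzing across different analysis sets is to demonstrate robust study results across the various alternatives".

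The Sample size section gives the expected losses: "Missing data and annual attrition were estimated to be 15% and 5%, respectively".

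**The concern.** Scoring all time after dropout as free of progression is a strong assumption, and it fits poorly with the rest of the protocol. The Background describes joint damage that accrues early in most patients and can continue despite good clinical control. The Sample size section plans on 36% progression by MRI and 25% by X-ray. A rate of zero after dropout agrees with neither.

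Three consequences follow for the progression endpoint:

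- Each arm's proportion is pulled downward, unless no dropout would have progressed.
- Outcomes that nobody observed enter the analysis as if known, so the precision is overstated.
- Leaving the study is scored as the good outcome, so if the arms lose patients at different rates, the arm that loses more gains an unearned advantage.

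Multiple imputation, which could avoid much of this, is planned but has no stated standing. If the two approaches disagree, only the link between the rule and the intent-to-treat analysis suggests which one counts.

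**Working it through.** **Inputs from the protocol article**
- Attrition 5% a year, missing data 15%, spontaneous remission 5%, about 45 per group before inflation, 62 after (Sample size).
- Progression 36% (MRI) and 25% (X-ray) (Sample size). These are planning rates for each imaging method, used here only as plausible levels of true progression.
- Scans at weeks 26, 52, 78 and 104 after baseline (Interventions).

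**1. The plan's own figure.** 45 / (0.95 × 0.85 × 0.95²) = 61.7, which rounds up to the stated 62. The plan therefore counts attrition separately from missing data, and counts both as lost information.

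**2. Share subject to the rule.** Two-year dropout is 1 − 0.95² = 9.75%, so about 62 × 0.9025 = 56 per arm are followed to the end.

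**3. Effect on the proportions.** Recorded progression = true progression × share captured.
- *Steady loss.* Assume dropout unrelated to progression, and progression spread evenly over the four scan intervals. Retention per half-year is √0.95 = 0.9747. Retention at the four scans is 0.9747, 0.9500, 0.9259 and 0.9025, with mean 0.938. Then 36% × 0.938 = 33.8% and 25% × 0.938 = 23.5%.
- *All of the dropouts' progression missed.* 36% × 0.9025 = 32.5% and 25% × 0.9025 = 22.6%.
- The 11.0-point gap between the two rates becomes 10.3 or 9.9 points. Power for that pair at 62 per arm goes from 26% to 24% or 23%.

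**4. Effect on the standard error** (all of the dropouts' progression missed). Compare √[q(1 − q)/62], where q is the recorded proportion, with √[p(1 − p)/(62 × 0.9025)], which is what the followed patients support.
- p = 0.36: 0.0595 / 0.0642 = 0.93.
- p = 0.25: 0.0531 / 0.0579 = 0.92.

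The standard error is about 7-8% too small. Part comes from counting 62 where 56 are followed (√(56/62) = 0.95), and the rest from the lowered proportion.

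**5. Unequal dropout** (assumed 5% against 15%, equal true progression of 36%, all of the dropouts' progression missed).
- Recorded: 36% × 0.95 = 34.2% against 36% × 0.85 = 30.6%, a false gap of 3.6 points.
- If only half of the dropouts' progression is missed, the gap is 1.8 points.
- For a two-arm comparison at 62 per arm (normal approximation, no multiplicity correction), the chance of wrongly favouring the arm with more dropout is 6.3% instead of 2.5%.
- At true progression of 25%, the gap is 2.5 points and the chance 5.2%.

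**The case against.** The strongest defence is that the effect is small and its direction between arms is hypothetical. With equal dropout unrelated to arm, both proportions fall by the same factor, the contrast moves towards zero and the test of no difference stays valid. All participants have both scans and allocation is concealed from them and from those treating them, so there is limited reason to expect unequal loss. Even the 3.6-point gap is only about 0.42 of the standard error of a two-arm difference, which is √(2 × 0.36 × 0.64 / 62) = 8.6 points. Most of this stands. It does not remove the downward bias in each arm's proportion or the overstated precision. Unequal loss is also not excluded: the sham arm always receives negative reports, and the imaging arms are expected to escalate treatment more.

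Four stronger readings are tempting, and the text does not support them:

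- *A quarter of participants are affected.* The rule names dropouts only. The 15% missing data is a separate quantity, and nothing says it is filled the same way. A missed interim scan need not lose progression, because later scans are compared with baseline or with the last detected progression.
- *Everyone who leaves gets the best outcome.* The wording, "dropouts will be assumed to have had no progression post-dropout", covers only the time after leaving, so progression already detected is kept.
- *Both co-primary endpoints are distorted.* The rule names progression. The article does not say how treatment escalation after dropout is handled, and that detail may sit in the full protocol or analysis plan.
- *The rule and multiple imputation contradict each other.* The rule is tied to the primary analysis, and imputation can be read as supportive. The fair criticism is that they are unranked.

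**Conclusion.** The point holds for the imaging-progression endpoint. The primary analysis uses an unexplained single-value rule that lowers progression proportions by about 6-10% in relative terms at the planned attrition, and understates an arm's standard error by about 7-8% where all of the dropouts' progression is missed. These sizes rest on 9.75% two-year dropout, the planning rates of 36% and 25%, and dropout unrelated to progression. If patients who leave are likelier to progress, the downward bias is larger.

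Bias in the comparison between arms, and the rise in one-sided error from 2.5% to about 6%, depend on the assumed 5% against 15% dropout. They show how exposed the analysis is and do not predict what will happen. At the planned attrition the effect is modest, so this is a cheap improvement of minor to moderate severity.

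**What to change.** Name one primary missing-data method for the progression endpoint. The natural choice is multiple imputation under missing at random, within arm, using earlier imaging scores, DAS28 and the minimization factors, with an imputation method suited to a binary endpoint. Report no progression after dropout and progression after dropout as two sensitivity bounds, and state that the imputed analysis decides.

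The cost is a little more analysis work: specifying an imputation model that fits the binary endpoint, and adding one bound that is not now planned. No new data are needed.

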### Data management

Data management and monitoring will use iDataFax® (Clinical DataFax Systems Inc., Hamilton, ON, Canada) and SAS/STAT version 9.2.

### Ethics

The study will be conducted in accordance with the principles of the Declaration of Helsinki and has been approved by the St Joseph’s Healthcare Hamilton Research Ethics Board (R.P. #09-3191). Informed consent will be obtained from each study participant.

## Discussion

The primary objective of the study is to investigate the relative value of MRI or X-ray over standard of care as tools to guide DMARD pharmacotherapeutic decision-making by rheumatologists for the care of RA and UIA. It is hypothesized that disease progression determined by MRI or X-ray will result in an increased rate of pharmacotherapeutic escalation. Recent evidence suggests that a proportion of RA patients persist with diagnostic imaging evidence of disease progression while in clinical remission [17].

The potential impact of this study is multifold. First, it will determine if there is value in implementing diagnostic imaging-guided pharmacotherapeutic clinical decision-making at the RA population level or whether further investigation in a targeted subset is warranted. The clinical trial literature is replete with trials demonstrating less than 50% of the population progressing on diagnostic imaging over 2 years [77,78]. However, predicting erosive progression is challenging [79,80]. In the current study, a health economic evaluation will be integrated within the trial and will contribute to the discussion on the value for money of this approach in a sample comprised of RA and UIA participants.

Second, the relative merits of MRI and X-ray as prognosticators in RA and UIA will be determined. The increased sensitivity of MRI for erosions that arise from the direct paired-bone comparisons is evident [14-17,29,30] but must be tempered by the increased false-positive rate for MRI erosions in healthy controls [47,81-83]. When the anatomies commonly imaged in practice are compared, the relative merits are less clear [14,15]. The probability of erosion is uniform neither by patient nor joint. In active disease, substantial erosive changes were noted in many patient joints, while others were spared [84]. These findings set the expectation that the greater number of bones and joints imaged on X-ray may negate the increased sensitivity of MRI in fewer joints. The advantages to imaging a greater number of joints needs to be taken into consideration with the increased demand on patients, cost, and false-positive rate. Further, the features measured for the X-ray and MRI interventions include more than just erosions and differ by modality. In RAMRIS, erosion score accounts for more than 69% of the total potential score [24]. The other MRI features measured are more transient than erosions and account for a minority of the total potential score: synovitis, the most transient, accounts for up to 10% of the total RAMRIS; edema accounts for up to 21% of the total score [24]. In contrast, vdHSS accounts for erosions and JSN. The former accounts 57% of the score for bilateral hands and wrists [45,46]. There is sufficient uncertainty in the relative prognostic merits of MRI and X-ray to argue the position of clinical equipoise in relation to the primary objective.

The merits of the proposed study should to be balanced with its limitations. To this end, the study population may be less than ideal. Challenges exist to adjusting diagnostic imaging evidence of disease progression for measurement reliability. The data used to estimate the sample size requirements were limiting. Other limitations may exist as well. The implications of these limitations and alternatives are discussed below.

First, the study population includes patients with varying degrees of disease activity. This may cause background noise to the signal of the intervention. The evidence that 19% of RA patients in clinical remission progress on diagnostic imaging over 1 year [17] may be limited to a small proportion of patients in clinical practice with quiescent disease. For the remainder of patients with active disease, treatment decision-making based on standard of care disease activity findings may be sufficient. In the presence of clinically active disease, attempts to link the effect of diagnostic imaging evidence of disease progression on treatment escalation may be confounded. The signal from the intervention may be dampened by the noise associated with standard of care treatment escalation. Ideally the study population would be characterized by a treat-to-target standard of care and limited to patients with low disease activity or in clinical remission to minimize the effect of standard of care on treatment escalation. In this trial setting, where the clinical practice use of disease activity measures is limited [40], the potential impact of diagnostic imaging guided care may be magnified.

Second, the application of the SDD has some limitations. In the current study, the inter-rater SDD will be used for simplicity. The SDD was used given that all image sets are to be scored independently. With the well characterized scoring systems used, the independent scoring of individual image sets carries less potential for bias from sources both known and unknown. The SDD will also be assessed at two separate time points to account for changes in inter-rater reliability and hence SDD over time. The approach does not account for intra-rater reliability. In addition, the lack of pairing image sets for the same patient may result in less sensitivity to change compared to alternatives. The smallest detectable change (SDC) is an alternative approach that uses paired images to assess reliability and change. Use of the SDC produces less variability, enabling smaller differences in disease progression to be detected [60]. Implementation of the SDC also carries incremental logistical complexity (for coordinating pairing) and rater scoring time. Acknowledging these tradeoffs, the SDD was proposed for the current investigation.

Third, for the sample size calculation, rates of disease progression were conservatively estimated from literature reports of disease progression between MRI and X-ray. Standard of care treatment escalation and a clinically meaningful effect size were not specifically accounted for in the estimate. Despite this limitation, the authors considered the sample size to be sufficient to resolve any incremental benefit of the interventions in the study population investigated.

A number of factors are expected to impact the relative merits of MRI and X-ray as prognostic tools in IA, including those affecting image resolution (for example, magnet strength to bore diameter ratio for MRI; number of views for radiography) and stage of disease. Measurement considerations including number of raters involved, their qualification and experience, number of readings and raters per image set, independent versus paired image rating, blinding the chronological order of image acquisitions, and current anti-rheumatic therapy are expected to affect the MRI and X-ray interventions equally.

This study represents an initial investigation into the clinical utility of MRI and X-ray in guiding anti-rheumatic pharmacotherapeutic decision-making for IA. The work will contribute to the knowledge of how diagnostic imaging may be leveraged to optimize rheumatologic care. Pending findings, future work will investigate the optimization of this intervention strategy, including but not limited to identifying population subsets at greatest risk, adjusting the interval over which imaging is conducted, testing in conjunction with a specific intensive DMARD clinical management strategy, and automated abnormality detection and quantification.

